### RA diagnosis

Diagnosing RA in patients to participate in the study will be done by a rheumatologist. Because the initial symptoms of the disease are not particularly distinctive, diagnosis of this condition can be delayed [34]. The American College of Rheumatology (ACR) has put forth criteria for the categorization of RA, which has a sensitivity of 91–94% and a specificity of 89% [35]. In 2010, the American College of Rheumatology unveiled a revolutionary new diagnostic criterion for the disease, based on which a definitive diagnosis of RA was dependent on receiving a score of 6 or more than 10. The diagnosis of the disease was largely determined by the number and type of joints affected, the levels of acute phase reactants, and the duration of the illness [36].

### Menopause

Menopause is defined as the permanent end of menstrual cycles, which is determined after a woman has gone 12 months without a period and there is no other underlying medical cause [37]. We will ask participants about the time of the beginning of menopause.

### Medications

RA patients use two drug lines to control their symptoms. The first line of these drugs, which are used to improve pain and inflammation in the acute phase of the disease in these patients, include aspirin, non-steroidal anti-inflammatory drugs, corticosteroids, and opioids [38]. The second line of drugs called disease-modifying antirheumatic drugs (DMARDs) are aimed at accelerating recovery by slowing down or stopping the progress of joint destruction and deformation, which include biological and non-biological drug groups [39]. In the current study, according to the inclusion criteria, patients should not change their drug regimen in the last 3 months and use non-steroidal anti-inflammatory drugs. Also, the use of biological and non-biological drugs is blocked in randomization.

### Adverse events

We will request that patients inform us of any adverse events that may have taken place during the study period; in case a participant experiences any rare adverse effects from the intervention or decides to discontinue the study for personal reasons, they will be removed from the study.

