Intermittent fasting (IF) diets have recently become popular for improvement in many chronic diseases [21]. IF is one of the types of fasting diet suggested by experts and various studies because the potential benefits of weight control, cardiovascular health, and oxidative stress reduction make it an attractive option [22]. This type of fasting refers to not consuming food or restricting its consumption in a certain period, for example, 16 h a day [23]. It seems IF can have positive effects on improving the autoimmunity in several autoimmune diseases [24, 25]. Likewise, with hormone secretion and oxidatively related gene expression, IF can protect against oxidative stress and has immunomodulatory effects [26].

Due to the pathophysiology of RA, and the autoimmune feature of this disorder, it seems IF may have beneficial effects on RA patients. Literature review showed most of the studies conducted in the field of fasting and RA have investigated total or subtotal fasting [27–30], or calorie restriction [31, 32]. To the best of our knowledge, there is no published study about the effects of IF in these patients around the world. Therefore, according to the limitations of complete fasting in the form of no food intake or restriction of calorie intake, and mentioning that this study is the first study that investigates the effects of IF in these patients, the present study will examine the effects of IF in postmenopausal, overweight, and obese women with RA in a randomized control clinical trial and parallel group manner.

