### Measuring the adherence to the diet

To encourage adaptation to the IF diet and to have a healthy food intake, during the intervention, all subjects will have weekly and monthly meetings with a nutritionist so that while the intervention group follows the IF diet, all the studied subjects will use the strategies for healthy food intake. In addition, all patients will be given written and verbal instructions for healthy diet recommendations, and as mentioned, there will be no disparity between the participants in the intervention and control groups. Monitoring of the fasting diet is done through the daily interaction of the researcher and the participant in the project (for example, through telephone conversations, taking a 3-day food record). The researcher will hold weekly telephone meetings with all participants to answer questions and check compatibility with the fasting diet in the intervention group. To measure the compliance of the people in the intervention group, if they do not attend more than two phone sessions in a row, or if they do not follow the fasting diet three times a week for more than two consecutive weeks, they are considered non-compliant. In addition, the researcher provides instructions on keeping accurate records of portion sizes and food items to the participants [33].

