### Interim analyses

Given the lack of any adverse effects observed in prior studies, no interim analysis or stopping rules are expected to be necessary for our current study of the IF diet.

*Plans to give access to the full protocol, participant-level data and statistical code*

It is possible to access the full details of the study protocol through IRCT.ir (IRCT20230217057441N1). The corresponding author can provide access to the data and participant datasets that were analyzed during the study.

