## Discussion

Previous studies show the effect of IF regimes on improving performance and strong resistance to a wide range of destructive mechanisms, including those that include metabolic and oxidative stress [55]. Insulin acts as the main stimulating hormone in the satiety state, glucagon acts as the main hormone in the fasting state, and the body uses the liver’s glycogen reserves to produce energy during fasting [56]. In the IF diet, a person repeatedly experiences satiety and hunger and the onset of negative energy balance in IF is when liver glycogen reserves are depleted, insulin levels decrease, glucagon levels increase, and fatty acids are metabolized to produce energy, which is usually more than 12 h after stopping food consumption and leads to autophagy, reduction of oxidative stress, improvement of metabolism, and increase of life span [57–59]. An umbrella study of meta-analyses conducted on the results of this type of diet on various factors showed improvements in CRP, TNF, and IL-6 factors in these patients [60]. A study by Uden et al. aimed at investigating the clinical performance of individuals and blood neutrophils in patients with RA after 7 days of complete fasting was conducted on 26 affected women and the results of this study showed a significant relationship between improving the inflammatory activity of joints and increasing the bactericidal capacity of neutrophils [58]. Also, a study that was conducted in 2010. The purpose of this study was to explore the alterations in intestinal microflora in individuals with RA when following a fasting or Mediterranean diet was conducted on 50 people with RA, and patients in the fasting group received about 300 calories during 7 days and the results of this study showed a significant decrease in the average score DAS-28 in both groups. Also, this study states that more studies are needed in the field of induced changes in fasting diet in patients with RA [59]. Moreover, a study was conducted to examine the effects of fasting or a ketogenic diet on serum levels of interleukin-6 and dehydroepiandrosterone sulfate in patients with RA. The results showed in addition that fasting had a positive effect on the serum levels of the investigated cases, and menopause as a confounding variable had an effect on the results of this study [29]. As noted, a large number of studies to evaluate the relationship between fasting and RA have investigated complete fasting, no food intake, or calorie restriction [27, 29, 30]. Despite the short-term positive effects of full or partial fasting with calorie restriction, this type of fasting is an impractical long-term strategy, as it should not be sustained for more than 7 days because it causes malnutrition in patients and its short-term positive effects are fleeting compared to the chronic nature of RA. Clinical and laboratory measurements tend to show improvement within a few days of beginning a fast and worsen upon resumption of diet and intake of restricted foods. Therefore, although many studies have been conducted on the effects of complete or partial fasting with caloric restriction in patients with RA and the results of them showed the overall positive effect of fasting on the symptoms of RA, considering the limitations of complete fasting in the form of no food intake or limiting calorie intake, and mentioning that until today, no study has been conducted to investigate the effects of IF in these patients in the world and Iran, this study will be conducted.

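### Adverse events depend on patients reporting them, while the weekly calls to both arms ask specifically only about the fasting diet, so counts may not be comparable between arms

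*Protocol article*

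**What the plan says.** All references are to the protocol article.

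- **Adverse events.** The method is a request to patients: "We will request that patients inform us of any adverse events that may have taken place during the study period". The same section anticipates harms from the diet: "in case a participant experiences any rare adverse effects from the intervention or decides to discontinue the study for personal reasons, they will be removed".
- **Measuring the adherence to the diet.** "The researcher will hold weekly telephone meetings with all participants to answer questions and check compatibility with the fasting diet in the intervention group".
- **Intervention.** Participants are telephoned weekly. The enquiry described is into difficulties in keeping to the IF diet, with guidance given where needed.
- **Randomization.** Patients, doctors and researchers all know the allocation.
- **Primary outcomes and Secondary outcomes.** No adverse-event outcome is listed.
- **Interim analyses.** "Given the lack of any adverse effects observed in prior studies, no interim analysis or stopping rules are expected to be necessary".
- **Background.** To the authors' knowledge, "there is no published study about the effects of IF in these patients around the world".

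**The concern.** If the patient has to take the initiative, events that she thinks trivial, or unrelated to her diet, tend to go unreported. That affects both arms. The second problem affects them differently. A weekly call that explores trouble with fasting gives an IF participant a regular occasion to mention headache, dizziness or a flare. A control participant on the same schedule has an opportunity to ask questions, but no corresponding enquiry is described. Because allocation is known to everyone, nothing else in the design evens this out.

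At stake is whether a list of adverse events by arm can be read as a comparison. The authors describe the trial as the first of IF in this population, so readers will look at that list even though safety is not a formal outcome.

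There is also a wording problem. The statement used to dispense with interim analysis and stopping rules is absolute, and it sits awkwardly beside two other sections.

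**Working it through.** The plan states no figure for adverse events, so there is none to reproduce. The check sets the contacts side by side, counts them, and asks what uneven reporting does to a comparison.

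**1. What each contact asks, and of whom**

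| Contact | Who | Stated purpose |
|---|---|---|
| Request to report adverse events | Patients, no arm specified | Any adverse event; timing and frequency of the request not given |
| Weekly call (Intervention) | Participants | Difficulties in complying with the IF diet |
| Weekly call (Measuring the adherence to the diet) | All participants | Answer questions; check the fasting diet in the IF arm |

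The contact schedule is the same for both arms. The specific enquiry is not: its subject exists only in the IF arm.

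**2. Number of calls already planned**

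Inputs: 22 per arm and 44 in total (Study sample size calculation); 8 weeks (Study design and participants); one call per participant per week. Assuming no dropout:

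- per arm: 22 × 8 = 176 calls
- total: 44 × 8 = 352 calls

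**3. Effect of uneven prompting**

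Let *p* be the true proportion of participants with an event in an arm, and *c* the chance that such an event reaches the team. Then

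expected reported count = 22 × *p* × *c*,

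and, with equal arm sizes,

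ratio of reported counts (IF to control) = (*p*_IF / *p*_C) × (*c*_IF / *c*_C).

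If the true rates are equal, the ratio is *c*_IF / *c*_C: it measures the prompting and not the diet. The article gives neither *p* nor *c*, so the ratio cannot be calculated, and it could not be recovered at analysis. Its direction is also open. Enquiry made only of IF participants may raise *c*_IF, while reliance on patients' initiative may lose events in either arm.

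For scale only, with assumed true rates of 1% to 10% and complete capture, the expected number of affected participants per arm runs from 22 × 0.01 = 0.22 to 22 × 0.10 = 2.2; at 5% it is 1.1. One event missed in one arm, or prompted in the other, would be large against such counts. The counts are small because the trial is small; what matters here is that the prompting should be the same.

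**4. The statement about earlier studies**

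- Interim analyses: earlier studies showed no adverse effects of any kind, with no population named.
- Adverse events: rare adverse effects of the intervention are foreseen.
- Background: no published study of IF in these patients is known to the authors, and "most of the studies conducted in the field of fasting and RA have investigated total or subtotal fasting" or calorie restriction.

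On the Background's account, the earlier studies cannot be studies of IF in RA. They may be studies of IF in other populations, in which case the sentence needs to say so. An unqualified absence of adverse effects also fits poorly with a section that expects rare ones.

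**The case against.** The strongest reply is that this is a condensed article which points to a fuller protocol at the registry. Event forms, timing, grading, and recording of onset and severity may be set out there, and their absence here is no finding. That stands. It is also true that the request to report is not limited to one arm, that nothing shows it is not repeated on the weekly calls, and that the IF-specific element is a compliance check and not an adverse-event question. So uneven prompting is a risk that follows from the text, not something the text states. What remains is that the article does describe what the calls are for. The described content differs by arm, and a common adverse-event enquiry is not part of it.

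A reader might infer four stronger things, none of which the article supports:

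- *That passive collection was chosen because earlier studies showed no harms.* That premise is offered only for having no interim analysis or stopping rules. The Adverse events section gives no reason for its method.
- *That the Discussion flatly contradicts the premise.* Its remark that "it should not be sustained for more than 7 days because it causes malnutrition in patients" concerns full or partial fasting with calorie restriction, which the authors contrast with IF.
- *That zero events among 22 IF participants shows the size of the problem.* The one-sided 95% upper limit, 1 − 0.05^(1/22) = 12.7%, is correct arithmetic. It holds equally with perfect reporting, so it reflects the sample size, and a better question would not change it.
- *That the trial makes a safety claim it cannot support.* The low-risk description in Oversight and monitoring explains why there is no separate data monitoring committee. The remark in Strengths and limitations about ready implementation is followed by a condition: improvement in symptoms and further studies.

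**Conclusion.** The point holds as a modest one about method. As described, adverse events reach the team on the patient's initiative, while the regular calls enquire specifically only about the fasting diet, in an unblinded trial. Counts by arm would then carry a risk of under-reporting and of uneven prompting, and would not be reliably comparable. The size and direction of the bias cannot be derived from the article. The conclusion assumes that the calls are run as described, without an adverse-event question common to both arms; if the full protocol already has one, the article need only say so.

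The statement in Interim analyses is a separate and smaller matter. It is too absolute beside the Adverse events section and has no basis in RA according to the Background. It is an unsupported premise that needs qualifying, not a proven contradiction. This does not imply that the decision on interim analysis or stopping rules is wrong.

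**What to change.** 1. On the weekly calls already planned, put one identical open adverse-event question to every participant in both arms, asked before and apart from the check on the fasting diet. Report adverse events descriptively by arm.
2. In Interim analyses, state which populations and which kind of fasting the remark about earlier studies refers to, and bring it into agreement with Adverse events and Background.

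The cost is a slightly longer call, on about 352 calls, and one extra table. No visit, staff or measurement is added. The common question makes the prompting equal; it does not remove differences in reporting that arise because participants know their allocation, so the table should be read descriptively.

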### Assessment of food intake

Assessment of food intake through 24-h food recording (including two working days and one day off) will be taken from participants during the intervention at the beginning, weeks 2, 4, 6, and 8. These registers will be taken by an experienced and trained expert and after the process of the data obtained from the food registers, the average intake of food items in these registers will be calculated and will be expressed as grams per day. Then, participants’ nutrient intakes will be calculated by entering these data into Nutritionist4 (N4) software.

### Assessment of physical activity

To carry out this project, physical activity records that can be used for ages 15–70 are used. Participants will fully record all their activities during the day. The start time, end time, and intensity of each type of activity will be recorded. The total duration of all participant’s recorded activities should be about 24 h. Then, the obtained data will be reported in terms of average MET-Hour per week.

### Anthropometric assessment

Anthropometric measurements including body weight, height, waist circumference, and BMI calculation (by dividing weight (kilograms) by the square of height (meters)) will be done. Body weight will be measured using a digital scale with minimal clothes and no shoes with an accuracy of 100 g. The standing height of people will be measured using a standard height meter, without shoes, and with an accuracy of 0.5 cm. A tape measure will be used to accurately measure the waist circumference to the nearest 0.5 cm, located midway between the supra iliac bone and the last rib.

### Health and disability assessment

HAQ-DI is widely regarded as the go-to tool for evaluating the functional capabilities of individuals with RA [40], and clinical variables are strongly associated with joint replacement, work disability, and mortality [41]. The reliability and validity of this questionnaire have been proven in the Iranian population [42]. HAQ was one of the first tools based on general and patient-oriented dimensions [43] and HAQ-DI is the main component of the HAQ, which was developed and validated in the late 1970s under the auspices of the Stanford Arthritis Centre [44]. HAQ-DI was developed by analyzing different questions and components from existing instruments at the time and was designed to provide a model of patient-centered outcome assessment and has an important role in many different fields including predicting successful aging, inversion pyramid therapy in RA, and investigating the risk of mortality in RA [44]. This survey consists of 20 questions divided into 8 functional categories, including dressing, grooming, rising, eating, walking, personal hygiene, lifting, and grabbing (objects) and outdoor activities. Each question is rated on a scale of 0–3, where 0 represents “no problem” and 3 represents “can’t do.”

### Assessment of inflammation and pain

VAS-pain questionnaire will be used to evaluate the pain level in patients. This tool is widely employed to assess pain levels, in which the patient is asked to rate the intensity of pain experienced measured on a 100-mm horizontal line with anchor-like descriptors in the pain field including “no pain” and mark the “worst imaginable pain” on two lines, and then measure it from the left edge (= VAS score) [45]. CDAI will be used to evaluate inflammation in these patients. To measure this index, the total scores of four criteria TJC28, SJC28, and PGA with a scale of 0 to 10 cm including “very good” and “very bad” along two horizontal lines and overall disease activity assessment (EGA) with a scale of 0 to 10 cm including “very good” and “very bad” along two horizontal lines will be calculated. Finally, the points will be classified as below [46]:

≤ 2.8 disease recovery

> 2.8 to 10 low disease activity

> 10 to 22 moderate disease activity

> 22 high disease activity

DAS-28 criterion will be used to evaluate the level of disease activity in patients. DAS28 score will be counted using TJC28, SJC28, CRP, and VAS disease activity (0–100 mm) of the patient. The following mathematical formula is used to calculate the overall score:$$\textrm{DAS}28\textrm{- CRP}={0.56}^{\ast }\ \left(\textrm{TJC}28\right)+{0.28}^{\ast}\left(\textrm{SJC}28\right)+{0.36}^{\ast}\ln \left(\textrm{CRP}+1\right)+{0.014}^{\ast}\textrm{VAS}+0.96$$

DAS28 score can vary from 0 to 9.4 and its interpretation is according to the following data [47]:

> 5.1: High disease activity

Between 3.2 and 5.1: moderate disease activity

Between 2.6 and 3.2: low disease activity

< 2.6: disease recovery

CDAI and DAS-28 criteria have been proposed in the latest update of the American Rheumatology Association in 2019 as valid and reliable criteria for an evaluation of RA patients [48].

To evaluate the duration of morning joint stiffness, the morning stiffness duration questionnaires and the degree of stiffness perceived by the patient will be used. Morning stiffness duration questionnaires will include options of less than 15 min, less than 30 min, less than 60 min, less than 90 min, and more than 90 min. The degree of perceived stiffness will also be determined by choosing on a scale of 0 to 10 cm, including “no stiffness” and “the highest degree of stiffness” along two horizontal lines [49].

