**Fig. 1 Fig1:**
[figure not shown]
Standard Protocol Items: Recommendations for Interventional Trials (SPIRIT) chart of the enrollments and assessments during randomized controlled trials

Inclusion criteria are menopause women with a body mass index between 25 and 35 kg/m^2^, age range between 50 and 70 years, diagnosed with RA by a specialist for more than 6 months, have moderate to low RA disease activity (i.e., disease activity score <5.1), following a stable drug regimen for 3 months before the intervention, not receiving non-steroidal anti-inflammatory drugs (NSAIDs), and more than 7.5 mg of corticosteroids, and willingness to cooperate. Exclusion criteria are consumption of alcoholic beverages, suffering from other autoimmune diseases, kidney diseases, pancreatitis, gallstones, cancer, pregnancy, and breastfeeding, following a special diet in the last 3 months, changing the drug regimen from 3 months before the intervention. Figure 2 demonstrates the flow diagram of the project.

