#### Secondary outcomes

Secondary outcomes are the changes in erythrocyte sedimentation rate (ESR), C-reactive protein (CRP), disease activity score in 28 joints (DAS-28), Visual Analogue Scale pain intensity (VAS-pain), level of total oxidant and antioxidant capacity (TOC and TAC), oxidative stress index (OSI), tender joint count (TJC), swollen joint count (SJC), tender-swollen joint count difference (TSJD), morning stiffness count (MS), patient global assessment of disease activity (PGA), global assessment of disease activity (EGA), and clinical disease activity index (CDAI) from baseline values.

We will evaluate both primary and secondary outcomes two times, first after the run-in period, at the beginning of the intervention, and second, 8 weeks later.

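### The printed DAS28-CRP formula uses untransformed joint counts and contradicts the score range and cut-offs stated beside it

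*Protocol article*

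**What the plan says.** Under Assessment of inflammation and pain, the protocol article names the components: "DAS28 score will be counted using TJC28, SJC28, CRP, and VAS disease activity (0–100 mm) of the patient". The formula that follows is

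DAS28-CRP = 0.56 × TJC28 + 0.28 × SJC28 + 0.36 × ln(CRP + 1) + 0.014 × VAS + 0.96,

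with no transformation of either joint count. The next sentence reads "DAS28 score can vary from 0 to 9.4 and its interpretation is according to the following data". The categories include "> 5.1: High disease activity" and "Between 3.2 and 5.1: moderate disease activity". Scores from 2.6 to 3.2 are low activity, and scores below 2.6 are labelled disease recovery.

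Two other places matter. Secondary outcomes lists the change in "disease activity score in 28 joints (DAS-28") among 14 unranked outcomes. The inclusion criteria, under Study design and participants, require that patients "have moderate to low RA disease activity (i.e., disease activity score <5.1"), without naming the version of the score. No other part of the article gives a DAS28 formula.

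**The concern.** A score built on 28-joint counts has a maximum that follows directly from its formula, and here that maximum is far above the one stated in the next sentence. If staff or the analysis program apply the formula as printed, joint counts carry much more weight than the cut-offs allow for. Patients whom the stated scale would place in the moderate band then score as high. Baseline levels and changes in DAS-28 would be on a scale to which 2.6, 3.2 and 5.1 do not apply. The same number, 5.1, also appears as the entry limit, so selection could be affected too if the same score is used there.

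**Working it through.** **Inputs.** The coefficients, the constant, the VAS scale (0 to 100 mm), the range and the cut-offs come from Assessment of inflammation and pain. Each count runs from 0 to 28 because the score covers 28 joints. The CRP unit and range for the formula are not given, so CRP values below are assumptions, varied from 0 to 300.

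**1. Can the stated range be reproduced from the printed formula?** No.
- Minimum, all inputs zero: 0.96 (stated: 0).
- Tender-joint term at its limit: 0.56 × 28 = 15.68, already above 9.4.
- Both joint terms: 15.68 + 0.28 × 28 = 15.68 + 7.84 = 23.52.
- Full score at 28/28, VAS 100, CRP 100: 23.52 + 0.36 × ln(101) + 1.40 + 0.96 = 23.52 + 1.66 + 1.40 + 0.96 = 27.54.
- The CRP assumption hardly matters: the maximum is 25.88 at CRP 0 and 27.93 at CRP 300.
- With CRP and VAS both zero, 16 tender joints alone give 0.96 + 0.56 × 16 = 9.92, and 11 tender plus 11 swollen joints give 0.96 + 0.84 × 11 = 10.20. Both exceed 9.4.

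**2. Do square roots on both counts remove the conflict?** At the upper end, yes.
- Joint terms at the limit: (0.56 + 0.28) × √28 = 4.44.
- Full score at 28/28, VAS 100, CRP 100: 4.44 + 1.66 + 1.40 + 0.96 = 8.47 (from unrounded terms).
- The maximum is 6.80 at CRP 0 and 8.86 at CRP 300. It reaches 9.4 only at a CRP of about 1350.
- The minimum is still 0.96, so the stated lower end of 0 is wrong under either form.

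**3. Which form agrees with the stated categories?** Take TJC 6, SJC 4, CRP 10, VAS 50.
- As printed: 3.36 + 1.12 + 0.86 + 0.70 + 0.96 = 7.00, high.
- With square roots: 1.37 + 0.56 + 0.86 + 0.70 + 0.96 = 4.45, moderate.
- The protocol's own CDAI, assuming PGA and EGA of 5 each: 6 + 4 + 5 + 5 = 20, which is moderate on its scale (above 10 to 22).

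In this example only the square-root form agrees with the other activity index.

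**4. Effect on a change score.** If TJC falls from 6 to 3 and SJC from 4 to 2, with CRP and VAS fixed:
- As printed: 0.56 × 3 + 0.28 × 2 = 2.24.
- With square roots: 0.56 × (√6 − √3) + 0.28 × (√4 − √2) = 0.40 + 0.16 = 0.57 (from unrounded terms).

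The printed form shows about four times the change.

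**5. Effect at 5.1, if the entry criterion uses this score.** At TJC 4, SJC 3, CRP 10, VAS 40 the printed form gives 5.46 (not eligible) and the square-root form 3.99 (eligible). At the same CRP and VAS, 307 of the 29 × 29 = 841 count pairs fall below 5.1 with square roots, and 277 of those 307 are at or above 5.1 as printed. This counts combinations, not patients, and says nothing of how often each occurs. The two forms agree only when both counts are 0 or 1; otherwise the printed form is higher, so the error can only run towards exclusion.

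**The case against.** **A lost root sign.** The strongest defence is that this is a printing loss and not the planned method. The brackets around the two counts would be natural after a root sign, and the sample-size equations in the same article are visibly damaged. This cannot be ruled out, and nothing shows that any score has been computed without roots. It does not clear the text, though. The logarithm, coefficients and constant are intact, the article presents this as the formula to be used, and it gives no correct version elsewhere.

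**The remedy is inferred.** No part of the article contains a square root for this score, and adding roots does not reproduce 0 to 9.4 exactly. That is fair: the contradiction is proved from the article alone, while the repair is supported by the upper limit and the CDAI example. The formula should therefore be checked against its cited source.

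**Eligibility.** A reader might infer that patients are being misclassified at entry. The article does not establish this. The inclusion criterion does not name DAS28-CRP. Run-in period places the CRP measurement after people have been selected, and Blood sampling and biochemical measurements has serum frozen until the assays are run. An earlier clinical CRP is not excluded, and 5.1 is the same limit, but the harm at entry remains conditional.

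**Weight of the outcome.** A reader might also take DAS-28 for a leading secondary outcome. Secondary outcomes gives no ranking, and CDAI does not use this formula.

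**A lower entry limit.** The activity scale labels scores below 2.6 as disease recovery, while the criterion speaks of moderate to low activity and sets only an upper limit. A reader might infer that entry should start at 2.6. The documents support only reconciling the wording; they do not fix a lower limit.

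**Conclusion.** The point stands. The printed formula, the stated range and the stated cut-offs cannot all be right: the formula reaches about 26 to 28 (CRP 0 to 300 assumed), nearly three times the stated maximum of 9.4. Applied literally, it inflates the DAS-28 secondary outcome, in the worked change by a factor of about four, and puts it on a scale to which the categories do not apply. Missing square roots are the likely cause. The conclusion about the outcome depends on the formula being used as printed; the conclusion about entry depends further on the 5.1 limit referring to this score. The primary outcome and the sample size do not use DAS28 and are not touched.

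**What to change.** - Check the formula against its cited source and restore the square roots: 0.56 × √TJC28 + 0.28 × √SJC28 + 0.36 × ln(CRP + 1) + 0.014 × VAS + 0.96.
- Correct the stated minimum, which the constant makes 0.96.
- Recompute from the raw components any DAS28 score already derived with the printed form, including screening scores if it was used there.
- State which score the entry limit of 5.1 refers to.
- Reconcile the moderate-to-low wording of the inclusion criterion with the activity categories. How this is resolved is for the sponsor.

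The cost is one formula, one range and one clarified eligibility line, plus a re-run of the score if it was already programmed. The joint counts, CRP and patient VAS are collected anyway, so no new measurement is needed. Recomputing cannot bring back anyone turned away at screening on a wrongly computed score, so whether that happened should be settled first.
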